### Recruitment{15}

Patients with type 2 diabetes who are attending the professorial unit medical clinic at the National Hospital of Sri Lanka (NHSL) will be invited to the study. An eligibility screen and a Montreal cognitive assessment (MOCA) will be performed in participants who volunteer. They will be randomized to meditation and waitlisted arms after obtaining informed written consent.

## Assignment of interventions: allocation

### Sequence generation {16a}

Patients will be randomized to meditation and waitlisted arms with a one-to-one allocation ratio using block randomization of 10 according to an online random number generation program.

### Concealment mechanism {16b}

Sealed envelopes will be prepared in advance, indicating the allocation of each patient according to the recruitment number. At the time of recruitment, the envelopes indicating the allocation will be provided to the researchers who will enrol patients. Thereafter, those who satisfy inclusion and exclusion criteria and give informed consent, will be assigned a unique patient recruitment number in chronological order. The sealed envelope with the allocation for the given recruitment number is opened, and accordingly patients will then either start the meditation programme or be allocated to the waitlisted arm.

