### Study setting{9}

The study will be conducted in a single centre; the National Hospital of Sri Lanka (NHSL), which is a tertiary care hospital. Patients with type 2 diabetes who are attending the professorial unit (academic unit) medical clinic at NHSL are invited to participate in this study. All physiological testing will be carried out in the Department of Physiology, Faculty of Medicine, University of Colombo.

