### Implementation {16c}

A member of the study team not involved in patient recruitment will generate the allocation sequence for assigning participants according to generated random numbers.

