## Assignment of interventions: blinding

### Who will be blinded {17a}

Data analysts and laboratory staff analysing samples and performing tests will be blinded to the allocation. The trial participant and the investigators will not be blinded due to the nature of the intervention.

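### One published block size of 10 in an open-label, single-centre trial, with sealed envelopes given to the enrolling researchers before eligibility and consent are complete, lets a recruiter who counts know about one allocation in six

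*Protocol article*

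**What the plan says.** All of the relevant text is in the Protocol article.

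- **Sequence.** Sequence generation {16a} specifies a "one-to-one allocation ratio using block randomization of 10 according to an online random number generation program". It mentions no varying sizes and no strata.
- **Setting.** Study setting {9}: "The study will be conducted in a single centre". With no strata stated, there is one running sequence.
- **Who knows past allocations.** Who will be blinded {17a}: "The trial participant and the investigators will not be blinded due to the nature of the intervention". Blinding covers data analysts and laboratory staff. The informed-consent section {26a} has the investigators take consent.
- **Custody.** Concealment mechanism {16b}: "At the time of recruitment, the envelopes indicating the allocation will be provided to the researchers who will enrol patients". The next sentence reads: "Thereafter, those who satisfy inclusion and exclusion criteria and give informed consent, will be assigned a unique patient recruitment number in chronological order".
- **Safeguards.** The envelopes are sealed and prepared in advance. After numbering, "The sealed envelope with the allocation for the given recruitment number is opened". Implementation {16c} adds: "A member of the study team not involved in patient recruitment will generate the allocation sequence".
- **Judged entry criteria.** Eligibility criteria {10} include willingness to take part, commitment to the three-month programme and, as an exclusion, inability to come to the weekly sessions.

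**The concern.** In permuted blocks, the allocations late in a block follow from the earlier ones. Three things are needed to exploit this: knowing the block size, knowing the earlier allocations, and having some discretion over who is enrolled next. Here the size is single and published. The earlier allocations are visible because the trial is open-label at one site. The discretion comes from criteria that rest on a recruiter's judgement. Giving the envelopes to the same researchers before screening and consent are finished removes a natural separation between those who enrol and those who release the allocation.

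What is at stake is selection. A recruiter who knows that the next place is waitlist could postpone a keen patient until a meditation place comes up. The arms would then differ in motivation. The article's own background links meditation's benefit partly to compliance with diet, exercise and medication, so a difference in motivation could plausibly reach HbA1c. Blinding the laboratory protects the measurement but does nothing about who enters which arm.

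**Working it through.** The article gives no figure for predictability, so there is none to reproduce.

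**Inputs.** Block size 10, 1:1 (Sequence generation {16a}); one centre (Study setting {9}); 172 patients (Abstract, and 86 per arm in Sample size {14}). **Assumptions.** The recruiter knows the block size and all earlier allocations, and there is one unstratified sequence.

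**Step 1: allocations known with certainty.** In a block of 2m with m per arm, the rest of the block is known once either arm is full. The expected number known in advance is 2m/(m+1). With m = 5 this is 10/6 = 1.67 per block, or 16.7%.

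The same result follows position by position. The last j places are all known when they belong to one arm, with probability 2·C(10−j, 5)/C(10, 5), where C(10, 5) = 252:

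| Last j places | Probability known |
|---|---|
| 1 | 2·126/252 = 1.000 |
| 2 | 2·56/252 = 0.444 |
| 3 | 2·21/252 = 0.167 |
| 4 | 2·6/252 = 0.048 |
| 5 | 2·1/252 = 0.008 |

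The sum is 1.667. Over the 17 full blocks in 172 patients, 17 × 1.667 = 28.3, so about 28 of 170.

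**Step 2: best guess.** Always naming the arm with more places left gives m + (2^(2m)/C(2m, m) − 1)/2 correct guesses per block. With m = 5 this is 5 + (1024/252 − 1)/2 = 6.53 of 10, or 65.3% against 50% by chance.

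**Step 3: is 10 the problem?** The same formulas for other fixed, known sizes:

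| Fixed block | Certain | Best guess correct |
|---|---|---|
| 4 | 33.3% | 70.8% |
| 6 | 25.0% | 68.3% |
| 8 | 20.0% | 66.6% |
| 10 | 16.7% | 65.3% |

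A smaller fixed block is worse. The weakness is that the size is fixed and known.

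**Step 4: varying sizes.** These figures come from simulating 172 patients with sizes drawn at random. The recruiter is assumed to know the set of sizes but not their order, which is a pessimistic assumption if the sizes are kept from recruiters.

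| Scheme | Certain | Best guess correct |
|---|---|---|
| Fixed 10 | 16.5% | 65% |
| 4, 6, 8 mixed | about 2% | 68% |
| 8, 10, 12 mixed | about 1% | 65% |

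The simulated 16.5% is slightly below the exact 16.7% because the last two of the 172 patients start an incomplete block. Mixing sizes removes most of the certainty. It does not lower the best-guess rate, because naming the arm that is currently behind works without knowing the block size. Mixing in smaller blocks raises that rate.

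**The case against.** The strongest reply is that concealment is better than a quick reading suggests. The envelopes are sealed, each belongs to a chronological recruitment number, and each is opened only after eligibility, consent and numbering. The Recruitment section {15} likewise puts randomisation after screening and consent. A non-recruiter generates the sequence. All of this stands. It makes the handover a weakness of custody and rules out calling it disclosure of the next arm. It does not answer the counting problem: sealing does not hide the earlier allocations, and numbering does not stop a recruiter from choosing when a patient receives the next number.

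It can also be said that willingness and commitment are required in both arms, that entry HbA1c is confined to 7 to 8%, and that the outcomes are analysed by multiple regression. These limit how far the arms could drift apart. They do not remove differences in motivation among eligible patients, which is not listed as a measured variable.

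Three stronger readings are tempting and are not supported.

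- **That allocation is fully predictable because recruiters hold the envelopes.** This presumes tampering. It could be said of any sealed envelopes held on site, and re-ordering is constrained because each envelope belongs to one number.
- **That the sequence generator has no part at allocation.** Implementation {16c} gives that person the sequence and says nothing either way about release. Concealment mechanism {16b} does not name who prepares or hands over the envelopes, or say whether they are handed over together or singly.
- **That a bias in HbA1c has been shown.** The figures measure predictability only.

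An article may leave details such as envelope opacity to the full protocol, and their absence is not held against it. The single block size and the delivery of envelopes to recruiters are stated rules.

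**Conclusion.** The point holds as a moderate, correctable weakness. If the plan is followed as written, a recruiter who keeps count knows about 16.7% of allocations before enrolling the patient (about 28 of 170) and can guess 65.3% correctly. This rests on the recruiter knowing the published block size, seeing all earlier allocations at the one site, and there being no undisclosed strata. Harm also requires the recruiter to act on that knowledge, and nothing in the document suggests that anyone has or will. The size of any effect on HbA1c cannot be derived from the document. The change is worth making because recruitment is described as under way, with a planned end of 30 June 2023, and selection that has already happened cannot be reliably undone in the analysis.

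**What to change.** 1. **Sequence generation {16a}.** For the patients still to be randomised, issue a new list with randomly varying block sizes that are not disclosed to recruiters and are not smaller on average than now. Sizes 8, 10 and 12 cut certain allocations to about 1% and leave the best guess at about 65%. Sizes 4, 6 and 8 are a poorer choice because the best guess rises to 68%. Start the new list when a current block is complete.
2. **Concealment mechanism {16b}.** State that a team member not involved in recruitment keeps the sealed, numbered envelopes and releases the next one only after the patient's eligibility and consent are logged. The person who already generates the sequence could do this.

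**Cost.** A new list, a change of custodian using existing staff, one contact per allocation, and the ethics and registry notification that the article already requires for amendments. The arms may end slightly unequal: an incomplete block of 12 can be out by at most 6 patients, whereas 172 patients in blocks of 10 can be out by at most 2 (17 full blocks plus 2 patients). No endpoint, sample size or patient burden changes. The part of predictability that comes from guessing remains, as in any blocked design.

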### Implementation {16c}

A member of the study team not involved in patient recruitment will generate the allocation sequence for assigning participants according to generated random numbers.

## Assignment of interventions: blinding

### Who will be blinded {17a}

Data analysts and laboratory staff analysing samples and performing tests will be blinded to the allocation. The trial participant and the investigators will not be blinded due to the nature of the intervention.

### Procedure for unblinding if needed {17b}

Unbinding will only be done if there is a need to further analyse blood samples in case of erroneous results.

## Data collection and management

### Plan of assessment and collection of outcomes{18a}

The study will be conducted for a period of 6 months. Assessments will be conducted in the following manner at recruitment: screening (baseline), 3 months, and 6 months in both the intervention and waitlisted groups.

#### Measurement tools

##### Anthropometric measurements

BMI: Height is measured to the nearest 0.1 cm (maximum distance from heels to uppermost position on head while standing barefoot in full inspiration using a stadiometer).

Body weight is measured to the nearest 0.1 kg using a digital scale (Secca) while wearing indoor light clothing. BMI is calculated as weight in kg/height in m^2^.

##### Clinical examination

Blood pressure: blood pressure in the seated position will be measured after 10 min of rest using a Riester digital blood pressure monitor (Rudolf Riester, Germany). Blood pressure will be checked twice.

##### Laboratory investigations

FBS, HbA1c, lipid profile, fructosamine, fasting serum insulin and 24-h urinary free cortisol will be measured in an accredited laboratory. Fasting plasma glucose will be measured in a fully automated biochemistry analyser (hexokinase method), and the lipid profile will be measured by an enzymatic method. HbA1c will be analysed using a high-performance liquid chromatography (HPLC) method. Insulin resistance will be calculated with the homeostasis model assessment (HOMA) equation: fasting glucose (mg/dL)×insulin level (uU/mL)/405 [4].

##### Orocecal transit time

The gold standard method to assess gastric emptying is radioisotope scintigraphy [31]. However, due to the noninvasive and simple technique involved, we opted for the orocecal transit time(OCTT) assessment using a hydrogen breath analyzer. Furthermore, by using OCTT, in addition to gastric emptying we can assess small bowel motility, which has an impact on glucose absorption and thus glycaemic control. Although there are more advanced newer techniques, such as MRI scans and capsular endoscopy [32], to assess OCTT, due to the high cost, these tests cannot be used in our study.

#### Lactulose hydrogen breath test

The time interval between ingestion of test meal containing 10 ml of lactulose after overnight fast and rise in breath hydrogen 10 ppm above basal using hydrogen breath analyser (Gastrolyzer, Bedfont Scientific Ltd, UK) is a measure of orocecal transit time (OCTT) [33, 34].

A solution including 10 g of lactulose in 100 mL of water will be administered. The breath test is performed at 10-min intervals, and a rise in hydrogen concentrations ≥10 ppm (particles per million) compared to baseline followed by at least two other subsequent rises are taken as OCTT. The OCTT in healthy subjects is between 40 and 170 min for a liquid diet [35].

##### Cardiac autonomic reflex assessment: CART

Autonomic functions will be assessed using Human Physiology AFT equipment (PL2604 by AD Instruments Pvt. Ltd, Australia)Heart rate response to deep breathing, which assesses beat-to-beat *R*-*R* variation during six breaths per minute paced slow deep breathing [expiration-to-inspiration ratio (*E*:*I*)=*R*-*R*_max_/*R*-*R*_min_].Heart rate response to standing is expressed as the ratio between the longest R-R interval (between the 20th and 40th beats) to the shortest R-R interval (between the 5th and 25th) after standing from the lying position [23].Valsalva manoeuvre and calculate the Valsalva ratio (maximum heart rate in phase II: minimal heart rate in phase IV)The blood pressure response after 3 min of standingThe blood pressure response to sustained hand grip

We will be recording a 15-min of resting ECG before the standard CART protocol. From which a 5-min recording [36] after the patient stabilizes, will be used for subsequent heart rate variation (HRV) analysis.

Spectral analysis of HRV, both time domain analysis and frequency domain analysis of the 5-min resting ECG tracing, will be performed using a Power Lab 8 data acquisition system [37]. The following parameters will be assessed according to the Task Force of the European Society of Cardiology and the North American Society of Pacing and Electrophysiology guidelines(1996) [38].

In time domain analysis, SDNN (standard deviation of normal-to-normal RR intervals), SDANN (standard deviation of the average normal-to-normal intervals for each 5-min segment of the ECG recording), SDNNI (mean of the standard deviation of all the normal-to-normal intervals for each 5-min segment of the recording), and RMSSD (root mean square of successive RR interval differences) will be analysed. In frequency-domain analysis, VLF (absolute power of the very-low-frequency band: 0.0033–0.04 Hz), LF (absolute power of the low-frequency band: 0.04–0.15 Hz), HF (absolute power of the high-frequency band: 0.15–0.4 Hz) and LF:HF (ratio of LF-to-HF power) [38] will be analysed. Pre- and post-meditation HRV analysis as well as any difference between the intervention and control arms will be compared. Furthermore, it has been shown that the cardiac vagal tone assessed using 5-min resting electrocardiogram recording has a good correlation with HRV analysis performed with 24-h recording in detecting subclinical cardiac autonomic neuropathy in patients with type 1 diabetes [39].

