#### Secondary outcomes

The effect on short-term and intermediate blood sugar control as measured by FBS and fructosamineThe effect of meditation on lipid profile.The effect of meditation on blood pressure.Analysis of the following possible mechanisms leading to changes in glycaemic and metabolic control in each arm (insulin resistance, autonomic functions, gut transit and 24-h urinary cortisol)

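### Two of the four time-domain HRV indices, SDANN and SDNNI, cannot add anything when HRV is analysed on a single 5-minute tracing

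*Protocol article*

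**What the plan says.** All the relevant text on the HRV method is in the Protocol article, under the heading on cardiac autonomic reflex assessment (CART).

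- Recording: "We will be recording a 15-min of resting ECG before the standard CART protocol".
- Portion used: "From which a 5-min recording [36] after the patient stabilizes, will be used for subsequent heart rate variation (HRV) analysis".
- Scope, stated a second time: "both time domain analysis and frequency domain analysis of the 5-min resting ECG tracing".
- Time-domain parameters to be analysed: SDNN, SDANN, SDNNI and RMSSD. Two of them are defined across segments: "SDANN (standard deviation of the average normal-to-normal intervals for each 5-min segment of the ECG recording" and "SDNNI (mean of the standard deviation of all the normal-to-normal intervals for each 5-min segment of the recording".
- Frequency-domain parameters: VLF, LF, HF and LF:HF.
- Use of the results: "Pre- and post-meditation HRV analysis as well as any difference between the intervention and control arms will be compared".

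The secondary outcomes place this work among the possible mechanisms: "insulin resistance, autonomic functions, gut transit and 24-h urinary cortisol". The Objectives section also names HRV analysis.

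**The concern.** SDANN and SDNNI summarise how the NN intervals behave across several 5-minute segments. The protocol gives them only one. On its own definitions, one index then has no usable value and the other is a second name for SDNN.

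What is at stake is the reading of the autonomic results. A column that is blank or all zeros will probably be noticed. A duplicate column may not be. If SDNN moves in favour of meditation, SDNNI will show the identical change and the identical p-value, and a reader could take it as separate support for an autonomic mechanism.

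**Working it through.** The protocol gives no numerical result on this point, so there is no figure to reproduce. The check applies its definitions directly.

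**Inputs (all from the CART section)**
- Length analysed: 5 minutes, extracted from 15 minutes recorded.
- Segment length in the definitions of SDANN and SDNNI: 5 minutes.

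**Number of segments**

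k = length analysed / segment length = 5 / 5 = 1.

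**SDANN.** With segment means m₁, …, m_k and their average m̄, SDANN = √[Σ(mᵢ − m̄)² / (k − 1)]. For k = 1 the numerator is 0 and the denominator is 0, so the value is undefined, with 0 degrees of freedom. If the software divides by k instead, the result is √(0/1) = 0 for every patient.

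**SDNNI.** With segment standard deviations s₁, …, s_k, SDNNI = (s₁ + … + s_k) / k. For k = 1 this is s₁, the standard deviation of all NN intervals in the tracing, which is SDNN. Hence SDNNI − SDNN = 0 for every patient at every visit.

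**Numerical illustration.** Two separate autocorrelated RR series were simulated around 850 ms. The inputs are arbitrary and serve only to show the identity.

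| Length analysed | k | SDNN (ms) | SDNNI (ms) | SDANN (ms) |
|---|---|---|---|---|
| 5 min | 1 | 31.45 | 31.45 | undefined (0 with divisor k) |
| 15 min | 3 | 42.49 | 41.67 | 9.17 |

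**Count.** SDANN and SDNNI are 2 of 4 time-domain parameters and 2 of 4 + 4 = 8 HRV parameters. SDNN, RMSSD, VLF, LF, HF and LF:HF do not depend on multiple segments.

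**If all 15 minutes were used.** Then k = 15 / 5 = 3 and SDANN rests on three means (2 degrees of freedom). Assuming normal, independent segment means:
- c₄ = 0.8862 for n = 3, so the sampling coefficient of variation is √(1 − 0.8862²) / 0.8862 = 0.523, about 52%.
- The 95% interval for the true value runs from √(2/7.378) = 0.52 to √(2/0.05064) = 6.28 times the estimate, where 7.378 and 0.05064 are the 97.5% and 2.5% points of chi-square on 2 degrees of freedom.

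**The case against.** The best counter-reading is that the recording mentioned in the definitions of SDANN and SDNNI means the full 15-minute trace, which contains three segments. This does not hold up. The text twice restricts HRV analysis to the 5-minute extract, and the second time it names time-domain analysis explicitly. The only 24-hour recording mentioned belongs to a cited study in type 1 diabetes, and the study schedule lists no longer recording. Had 15 minutes been intended, the section would contradict itself and still need correcting.

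Some points on the other side do stand:
- SDNNI on one segment is redundant rather than empty: it carries exactly what SDNN carries.
- The three-segment precision figures describe an analysis the protocol does not plan. They assume independence that adjacent segments of one trace may lack, and they concern precision within a patient, whereas arm comparisons average over patients. They bear only on the choice of remedy.
- The practical effect is small. Neither index is singled out as a key measure, and the fault would probably surface when the data are first exported.

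Nor is this a matter of detail that a condensed article leaves to a fuller document. The tracing length, the parameter list and the definitions are all stated, and they are incompatible.

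**Conclusion.** The concern holds, as a minor point. On the protocol's own definitions, SDANN on the planned tracing is undefined or a constant zero, and SDNNI is identical to SDNN. This is an algebraic identity that follows once HRV is computed on one 5-minute tracing; it depends on no assumption about the data. The effect is confined to 2 of 8 HRV parameters within a secondary mechanism outcome. The HbA1c primary outcome, the five reflex tests, the other six HRV parameters and the sample size are unaffected.

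**What to change.** Preferred: delete SDANN and SDNNI from the time-domain list and keep SDNN and RMSSD, with VLF, LF, HF and LF:HF, all from the 5-minute tracing. No informative measure is lost.

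Alternative: state that SDANN and SDNNI, and only these, use all three 5-minute segments of the 15-minute trace. The price is an SDANN based on three means, and the inclusion of time before the patient has stabilized, which the single-extract rule is meant to leave out.

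Either is a change of wording only and needs no extra recording.
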